# Permissive weight bearing in trauma patients with fracture of the lower extremities: prospective multicenter comparative cohort study

**DOI:** 10.1186/s12893-018-0341-3

**Published:** 2018-02-02

**Keywords:** Fractures of the lower extremities, Trauma patients, Complications, Permissive weight bearing

## Abstract

**Background:**

The standard aftercare treatment in surgically treated trauma patients with fractures around or in a joint, known as (peri)- or intra-articular fractures of the lower extremities, is either non-weight bearing or partial weight bearing. We have developed an early permissive weight bearing post-surgery rehabilitation protocol in surgically treated patients with fractures of the lower extremities. In this proposal we want to compare our early permissive weight bearing protocol to the existing current non-weight bearing guidelines in a prospective comparative cohort study.

**Methods/design:**

The study is a prospective multicenter comparative cohort study in which two rehabilitation aftercare treatments will be contrasted, i.e. permissive weight bearing and non-weight bearing according to the AO-guideline. The study population consists of patients with a surgically treated fracture of the pelvis/acetabulum or a surgically treated (peri)- or intra-articular fracture of the lower extremities. The inclusion period is 12 months. The duration of follow up is 6 months, with measurements taken at baseline, 2,6,12 and 26 weeks post-surgery.

Primary outcome measure: ADL with Lower Extremity Functional Scale. Outcome variables for compliance, as measured with an insole pressure measurement system, encompass peak load and step duration.

**Discussion:**

This study will investigate the (cost-) effectiveness of a permissive weight bearing aftercare protocol. The results will provide evidence whether a permissive weight bearing protocol is more effective than the current non-weight bearing protocol.

**Trial registration:**

The study is registered in the Dutch Trial Register (NTR6077). Date of registration: 01–09-2016.

## Background

The development of surgical fracture care boosted 50 years ago and is improving since, while emphasis on post-surgical care facilitating optimal bone healing and functional recovery remains low [1, 2]. The positive effects of early weight bearing, both for fracture healing and for maintaining muscle and bone mass, are well known. However, little is known about the association between a) the amount or timing of weight bearing and b) bony consolidation or functional recovery. As a result, weight bearing rehabilitation is often cautious and led by existing dogmas, such as the fear for secondary dislocation of the fracture or failure of a mechanical construct. The standard aftercare treatment in surgically treated trauma patients with fractures around or in a joint, known as (peri)- or intra-articular fractures of the lower extremities, is either non-weight bearing or partial weight bearing [3]. According to the AO Principles of Fracture Management, postoperative management of (peri)- or intra-articular fractures of the lower extremities consists of non-weight bearing for 6–12 weeks, followed by partial weight bearing with a 25% increase in weight loading every week [1]. However, in a study by van der Vusse et al. [4] among 111 trauma surgeons and orthopaedic surgeons in the Netherlands, it was shown that consensus about the weight bearing aftercare for tibial plateau fractures is limited. Furthermore, while instructions on rehabilitation provided to patients may be clear, patients’ compliance with a non-weight bearing or limited weight bearing regime has been found to be poor [5, 6]. A number of studies found that patients had actually exceeded the prescribed amount of partial weight bearing even though their self-reported compliance was high [6]. Thus, despite their willingness to comply, patients often do not adhere to the suggested restrictions on weight bearing and increase their weight bearing as fracture healing progresses.

We have developed an early permissive weight bearing post-surgery rehabilitation protocol, where progression of weight bearing is guided by the subjective experience (e.g. pain, weight bearing tolerance) of the patient and therapist, and objective parameters (e.g. temperature of the limb, edema, and gait parameters) are registered. This early permissive weight bearing protocol has previously been implemented and validated in our rehabilitation center since 2005. Follow up and evaluation of the permissive weight bearing protocol are ensured by recording and documenting weight bearing milestones (e.g. walking with 2 crutches, walking with 2 canes, walking with one cane and walking without any walking aids) in a database. Retrospective analysis of the complications that occurred while using this new protocol showed a complication rate of 10%, non-unions and infections being the most common complications. A comparison of our complication rate to data reported in literature that were based on protocols using the existing guidelines, such as the current non-weight bearing guidelines (AO protocol), showed lower complication rates for all our groups treated according to the permissive weight bearing protocol. Recent literature has reported composite postoperative complication rates of up to 37%, with an average of 10–20% in patients with lower extremity fractures [7–16].

In our study we want to compare our early permissive weight bearing protocol to the currently existing AO treatment guidelines in a prospective comparative cohort study. In addition to the follow up, featuring clinical documentation and registration of weight bearing milestones, new techniques for ambulatory measurements of loading (i.e. gait analysis by means of insoles) and non-invasive quantification of muscle mass will be used. This study will be performed in patients with (peri)- or intra-articular fractures of the pelvis/acetabulum and lower extremity after surgical treatment for which existing guidelines do not allow early full weight bearing in the first 6–12 weeks.

The primary research question is: How do the current guidelines (AO guidelines) and a permissive weight bearing protocol compare as to early recovery of functional outcome in trauma patients with fractures of the lower extremities after 6 months?

Secondary research questions are:To what extent is the use of a permissive weight bearing protocol for trauma patients with fractures of the lower extremities, as compared to treatment as usual (TAU), preferable in terms of costs, effects and utilities from both a hospital and a societal perspective?How do the current guidelines and a permissive weight bearing protocol compare as to complication rate in trauma patients with fractures of the lower extremities after 6 months?

### Hypothesis

#### Hypothesis 1

The permissive weight bearing protocol will lead to 1A: a better outcome at activity level (as measured with the Lower Extremity Functional Scale (LEFS)), 1B: a better early recovery at function level (as measured with the Brunnstrom Fugl-Meyer (BFM) test), 1C: a better participation (as measured with the SF-36) and 1D: a better quality of life (as measured with the EQ-5D-5L) in the first 6 months post-surgery, as compared to patients who are treated according to current standard guidelines. It is expected that in the long-term (i.e. 1 year) functional outcome will be similar between the treatment groups and will therefore not be the primary focus of this study [3]. We have chosen for the three scales mentioned above to cover the major outcome levels in the ICF model [17].

#### Hypothesis 2

The permissive weight bearing protocol for trauma patients with fractures of the lower extremities is more cost-effective compared to the non-weight bearing protocol and current guidelines.

#### Hypothesis 3

The rate of complications (e.g. failure of osteosynthesis, secondary displacement of fracture parts, non-union, infections) is equal or lower in patients who are treated according to the permissive weight bearing protocol compared to patients treated according to standard current guidelines.

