### Secondary outcome measures

Function (Brunnstorm Fugl-Meyer)Participation (SF-36)Improvement in quality of life (EQ-5D-5L)Reduction in health and society costs (RUM)Total complication rate

Outcome variables gauging functional outcome:Score on Brunnstrom Fugl-Meyer [21] at 0, 2, 6, 12 and 26 weeks post-surgeryScore on SF-36 [22] at 0, 2, 6, 12 and 26 weeks post-surgeryScore on EQ-5D-5L [23] at 0, 2, 6, 12 and 26 weeks post-surgery

Outcome variables gauging complication rate:Failure of the osteosynthesis, defined as loosening or breakage of implantsMigration of fracture parts, defined as > 3 mm articular step-off and/or varus/valgus malalignment > 5 degreesInfection, defined as (but not limited to) purulent wound drainage, inflammation, erythema, fever, increased white blood cell (WBC) count, increased C-reactive protein (CRP) and/or increased erythrocyte sedimentation rate (ESR), necessitating admission for intravenous antimicrobial treatment and/or revision surgeryNon-union, defined as no radiographic union achieved after 6 months or no progress in healing

Outcome variables gauging compliance [5, 6, 24–26]:Self-reported adherence to the fracture-related weight bearing protocol, will be recorded in medical records by physical therapists.Peak load (% body weight) and step duration (in seconds) as measured by the Sensistep [27] insole pressure measurement system. The Sensistep will be used by the patient only during daytime. The measurements with the Sensistep will continue until the patient has shown 100% weight bearing. The time for the latter to occur, may differ between patients.

Brunnstrom Fugl-Meyer: This is a test that evaluates the degree of synergy formation. The test consists of 55 test items that can be scored on an ordinal 3 - point scale (0–2 points). The total test consists of an examination of the upper extremity, an examination of the lower extremity and an examination of the balance. For our study we will only use the examination of the lower extremity. The maximum total score concerning the lower extremities is 34 points [21].

SF-36: This is a multi-purpose, short-form health survey with 36 questions. It yields an 8-scale profile of functional health and well-being scores, as well as psychometrics-based physical and mental health summary measures, and a preference-based health utility index. The higher the score the better the participation [22].

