### Statistical analyses

Data will be recorded in the digital study database and will be analyzed by a researcher blinded to the study groups the patients entered into.

Variations in case mix between centers can influence the interpretation of outcome data. Therefore, for each of the data sets collected, differences in outcome variable between the services will be tested using multiple MANCOVA’s, entering various indicators of case mix as co-variates (i.e. age, gender, ISS, number of complications, etc).

Insole pressures will be presented as mean ± SD. Statistical analysis of pressures involves repeated-measures two way ANCOVA using time as the within-group factor and treatment protocol as the between-group factor. Post-hoc group comparison at the different time points is only performed when the overall repeated-measures tests are statistically significant. A Bonferroni approach will be used to avoid spurious false positive findings. All scores will be tested for normality using the Shapiro-Wilk test. Multilevel factor analysis will be performed to determine independent factors related to the primary outcome parameter functional outcome.

Statistical analysis will be performed using the Statistical Package for Social Sciences (SPSS, IBM), version 23. Level of significance will be set at alpha< 0.05.

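### Hypothesis 3 claims equal or lower complications, but no margin is given and only difference tests are stated, so a non-significant result could be taken as confirming it

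*Protocol article*

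**What the plan says.** Under Hypothesis, the protocol article states that "The rate of complications (e.g. failure of osteosynthesis, secondary displacement of fracture parts, non-union, infections) is equal or lower in patients" on the permissive protocol, compared with current standard guidelines. Hypotheses 1 and 2 claim superiority; only Hypothesis 3 includes equality. The matching secondary research question in the Background is open: "How do the current guidelines and a permissive weight bearing protocol compare as to complication rate in trauma patients". Under Secondary outcome measures the endpoint is listed as "Total complication rate", with osteosynthesis failure, migration of fracture parts, infection and non-union as components.

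Under Statistical analyses, "differences in outcome variable between the services will be tested using multiple" MANCOVAs. Complications are named there only among the case-mix covariates: "age, gender, ISS, number of complications, etc". The threshold is given as "Level of significance will be set at alpha< 0.05". The article states no margin, no largest acceptable excess, no confidence-limit rule and no sample size for complications. The Sample size calculation rests on the LEFS alone.

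For rates, the Background reports that the centre's own retrospective analysis of the permissive protocol "showed a complication rate of 10%, non-unions and infections being the most common complications". It puts the literature average for lower extremity fractures at 10–20%, with composite rates of up to 37%.

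**The concern.** A claim that a rate is equal or lower needs either a largest tolerable excess fixed in advance or a commitment to report only an estimate. The article states a test of difference, and failing to reject a difference cannot support equality. MANCOVA is also a model for several continuous outcomes, not for whether a patient had a complication.

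Complications are the main safety question for early loading: the Background names fear of secondary dislocation and construct failure as the reason for cautious aftercare. If a study of this size finds no significant difference, that result could be cited as confirming Hypothesis 3 although the data remain compatible with a large excess.

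**Working it through.** **Inputs.** 51 per group needed and 134 recruited (Sample size calculation). Complication rates of 10% to 20% (Background). Alpha 0.05 (Statistical analyses); sidedness is not stated, so two-sided is assumed. The complication rate is taken as the proportion of patients with at least one complication. Clustering by hospital and covariate adjustment are ignored.

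**1. The plan's own figure.** There is no figure for complications to reproduce. The LEFS calculation uses 10% of 65 = 6.5 points and SD 10. At 80% power, n = 2(1.96 + 0.84)²(10/6.5)² gives 38 per group (39 by t-test), not 51. The value 51 matches 90% power (50 by normal approximation, 51 by t-test). The total follows as 102 × 1.2 × 1.1 = 134.6. The mismatch is a separate matter; 51 is used here as stated. The 67 per group below is 134/2, an upper bound that assumes no drop-out and equal groups.

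**2. Precision if both rates equal p.** Half-width = 1.96 × √(2p(1−p)/n). For p = 0.10 and n = 51: 1.96 × √(0.18/51) = 1.96 × 0.0594 = 0.116.

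**3. Chance of missing a doubling from p to 2p.** With p̄ = 1.5p, power = Φ{[p − 1.96√(2p̄(1−p̄)/n)] / √([p(1−p) + 2p(1−2p)]/n)}. For 10% v 20% and n = 51: (0.100 − 1.96 × 0.0707)/0.0700 = −0.55, so power is 29% and 71% are missed.

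| Rate p | Half-width, n=51 | Half-width, n=67 | Power for doubling, n=51 | Missed, n=51 | Missed, n=67 |
|---|---|---|---|---|---|
| 10% | 11.6 points | 10.2 | 29% | 71% | 63% |
| 15% | 13.9 points | 12.1 | 44% | 56% | 45% |
| 20% | 15.5 points | 13.5 | 60% | 40% | 28% |

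Exact enumeration of the chi-square test agrees (power 29%, 45% and 61% at n = 51). With Fisher's exact test the power is lower, at 20%, 36% and 53%. Detecting a doubling with 80% power would need 199, 121 and 82 per group.

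**4. Chance of excluding an excess of m.** The article gives no m, so 5 and 10 points are illustrations only. With equal true rates and one-sided 2.5%, power = Φ(m/√(2p(1−p)/n) − 1.96). At n = 51 and p = 10%: 39% for 10 points and 13% for 5 points. At p = 20%: 24% and 9%.

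If the permissive group truly does better, with 10% against 15% or 20% in controls, the same rule gives 63% or 82% for 10 points and 33% or 57% for 5 points.

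**The case against.** Several objections stand and limit the point.

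- A reader might infer that the plan will declare safety from a non-significant test. No section says so. The research question is open, and Hypothesis 3 can be read as a directional expectation for a secondary outcome. The supportable statement is that a null result could be taken that way.
- A reader might infer that Hypothesis 3 carries the recommendation for nation-wide introduction. The closing paragraph of the Discussion ties that to the protocol being more effective, not to equal complications.
- The article does not name complications as a MANCOVA outcome. The sentence covers each data set collected and is the only general outcome method given, so applying it to complications is a reading. Listing complications as a covariate is a related but separate problem.
- Sizing a study on its primary outcome is normal; low power for a secondary outcome is not in itself an error.
- A null result is not the likely outcome in every unsafe scenario. At a 20% control rate a doubling would be detected 60% of the time with 51 per group. If permissive weight bearing is truly safer, a 10-point excess can often be excluded.

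It can also be argued that the model and the margin sit in a fuller document that is not shown. That is fair for the model. It is weaker for the margin, because the hypothesis is stated here, is paired here with a test that cannot support it, and needs its margin before data are seen.

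**Conclusion.** The point holds as a mismatch between hypothesis and analysis: a claim that includes equality, no margin, and only difference testing stated, by a method that does not fit a yes/no outcome. As written, the plan cannot support the equality part of Hypothesis 3.

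At 51 per group, the chance of missing a doubling runs from 71% to 40% across the article's 10–20% range, so the warning is strongest at 10–15%. The unadjusted half-width is about 12 to 16 points over the same range; an expectation of 10 to 12 points would hold only at a 10% rate in both groups. These figures assume equal groups, a two-sided 5% test, independent patients and no adjustment. Clustering within the six hospitals would be expected to widen the intervals, but the article gives nothing from which to quantify this. The missing margin is certain on this document; misuse of a null result is a risk, not something the plan prescribes.

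**What to change.** - Restate Hypothesis 3 as an estimate: the risk difference in total complications with a 95% confidence interval, from a binomial or logistic model.
- Adjust for the case-mix variables already planned (age, gender, ISS), because groups are formed by hospital without randomization. Do not adjust for the number of complications, which is the outcome itself. At 10–20%, 102 patients would give only about 10 to 20 patients with a complication, so keep the covariates few and report the unadjusted difference alongside.
- State that a non-significant result will not be reported as equal.
- Allow the wording 'not higher' only if the upper 95% limit lies below a margin fixed and justified before data are seen. If no margin can be justified, report the estimate alone.
- State the expected unadjusted half-width: about 12 to 16 points at 51 per group for rates of 10% to 20%.

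The cost is a change of wording in Hypothesis 3 and Statistical analyses, and a weaker permitted safety claim. No extra patients are needed.

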## Methods/design

### Study design

This study is a prospective multicenter comparative cohort study in which two rehabilitation aftercare treatments will be contrasted, i.e. permissive weight bearing (PWB) and non-weight bearing (NWB) or the AO-guideline. The patient will be followed for 6 months (see Fig. 1). The inclusion time is 12 months.

**Fig. 1 Fig1:**
[figure not shown]
Flow chart of the study

Prior to participation, informed consent will be obtained from all participants.

This study has been approved by the Medical Ethics Committee of Maastricht University Medical Center, Maastricht, the Netherlands.

This study is registered in the Dutch Trial Register (NTR6077). Date of registration: 01–09-2016.

### Population

Trauma patients, aged 18 years or older, with a surgically treated fracture of the pelvis/acetabulum or a surgically treated (peri)- or intra-articular fracture of the lower extremities, where, according to the current guidelines, permissive weight bearing would not be allowed in the first weeks post-operatively, will participate.

Patients must be able to understand and follow instructions and written informed consent has to be obtained. Patients are screened for eligibility according to the inclusion and exclusion criteria presented in Table 1.

**Table 1 Tab1:** Inclusion and exclusion criteria

Inclusion criteria	Exclusion criteria
• Trauma patients with surgically treated (peri)- or intra-articular fractures of the lower extremities, i.e. pelvic fractures, acetabular fractures, distal femur fractures, tibia plateau fractures, pilon fractures and foot fractures. According to the AO fracture classification type A, B, or C. • Age > = 18 years • Being able to understand the questionnaires and measurement instructions	• Restricted mobility due to other causes than the surgically treated (peri)- or intra-articular fracture, i.e. bilateral fractures, amputations, or ipsilateral significant fractures that hamper mobilization. • Severe non-fracture-related comorbidity of the lower extremity, e.g. congenital bone and tissue disorders. • No additional problem of rheumatic orthopaedic or neurological nature of the lower extremities (e.g. primary coxarthrosis or gonarthrosis) • Congenital bone and tissue disorders. • No informed consent

Participants for the intervention group, i.e. who will receive treatment according to the permissive weight bearing protocol, will be recruited in Maastricht University Medical Center (Maastricht) and in Zuyderland Medical Center (Heerlen). This intervention has already been implemented in these two hospitals, as well as in Adelante Rehabilitation Center (Hoensbroek).

The control group will be recruited in Viecuri Medical Center (Venlo), Maxima Medical Center (Veldhoven), Catharina Hospital (Eindhoven) and Elkerliek Hospital (Helmond). All participating centers are located in the Netherlands. The inclusion of the participants will start in October 2017 and will continue until September 2018.

### Randomization process

Randomization is not considered feasible because of the nature of the two different interventions. Implementation of these different protocols includes patient instructions as well as physical therapy guidance and nursing staff participation. A mix of protocols to be used on a ward is therefore considered not optimal because of information bias.

### Feasibility

From the trauma registration in all the six hospitals, every year more than 500 patients are admitted for surgical treatment of these specific lower extremity fractures that require unloaded aftercare according to the current guidelines (AO protocol). Accounting for an informed consent ratio of 50% and a lost-to-follow-up rate of 20%, an inclusion phase of one year will be necessary to complete this study.

